### Trial design and description of the intervention

#### Original trial design

The study was initially designed as a factorial design randomized clinical trial whose primary aims were to determine whether (1) elastic compression stockings used for 2 years compared to inactive (placebo) stockings, and (2) celecoxib, a COX-II inhibitor, used for 30 days compared to placebo, were effective in preventing PTS in patients with symptomatic proximal DVT. The rationale for the use of a COX-II inhibitor was to assess whether an anti-inflammatory drug used acutely could limit the extent of venous valvular damage and reduce the frequency of subsequent PTS. However, in December 2004, The National Institutes of Health announced suspension of the use of celecoxib for all participants in a large colorectal cancer prevention clinical trial conducted by the National Cancer Institute, because analysis by an independent Data Safety and Monitoring Board (DSMB) showed a 2.5-fold increased risk of major fatal and non-fatal cardiovascular events for participants taking the drug compared to those on a placebo. As a result of this announcement, the SOX Trial Steering Committee decided on December 21, 2004 to discontinue the Celecoxib intervention of the SOX Trial [55]. This decision was made after independent meetings of the Steering Committee and the SOX Trial DSMB and was based on patient safety and also on study feasibility. The SOX Trial thus resumed in February 2005 as a parallel group randomized trial, i.e. without the celecoxib/placebo intervention.

#### Current trial design

The study is a randomized, allocation concealed, double-blind multicenter clinical trial with an intervention allocation ratio of 1:1 (figure 1 summarizes the study design). Once a patient is deemed eligible and consents to the study, the research nurse at each site logs onto a web-based interface which allocates the patient to one of 2 treatment groups: active stockings or inactive (placebo) stockings. Treatment group is assigned randomly using permuted blocks of randomly varying sizes at each study site to maintain close balance of the numbers in each treatment group, at any time during the trial, and to ensure allocation concealment. The active stockings intervention consists of knee-length, 30–40 mm Hg (Class II), graduated ECS worn on the DVT-affected leg daily, applied upon waking and removed upon retiring, beginning as early as possible within 14 days after DVT diagnosis and continued for 2 years. The inactive stockings intervention (the control intervention) consists of knee-length, inactive stocking (5 mm Hg compression at ankle; similar to store bought trouser sock), identical in appearance to the active stockings, worn on the DVT-affected leg daily, applied upon waking and removed upon retiring, beginning as early as possible within 14 days weeks after DVT diagnosis, and continued for 2 years. Active and inactive stockings are manufactured by SIGVARIS Corp.

**Figure 1 F1:**
[figure not shown]
Study architecture-Flow diagram: The SOX Trial.

#### Patient eligibility criteria

Patients presenting with a first, symptomatic, objectively confirmed proximal DVT diagnosed within the last 10 days (with or without concurrent distal DVT or pulmonary embolism), who have no contraindications to standard anticoagulant therapy and who provide informed consent are eligible for the study.

Patients are excluded if they 1) have a contraindication to compression stockings e.g. previously documented moderate to severe peripheral arterial disease of the lower extremities, absence of palpable pedal pulses or arterial compromise due to massive venous obstruction; 2) have a limited lifespan (estimated < 6 months); 3) have geographic inaccessibility preventing their return for follow-up visits; 4) demonstrate inability to apply stockings daily (e.g. severe arthritis, arm paralysis, and unavailability of a caregiver to apply stockings daily); or 5) were prescribed lytic therapy to treat their acute DVT.

#### Study procedures

Once the patient is recruited and randomized via the SOX Trial's web-based interface, the computer generates a unique treatment code for each patient, according to treatment group and center. The study nurse faxes the patient's leg measurements to the stocking supplier, who then ships the assigned pair of ECS to the patient (i.e. correct size, according to patient's measurements; active or inactive stocking, according to patient's treatment code). ECS are pre-packaged by the manufacturer in a plain box, labeled with the unique stocking code (i.e. patient and health personnel blinded). The same procedure is used to replace the patient's ECS every 6 months during the trial.

Several strategies are used to protect against bias, including: randomization with allocation concealment, enrolling consecutive patients, blinding subjects to treatment assignment, blinding investigators, study nurses and outcome assessors (e.g. vascular technicians, radiologists) to treatment assignment, strict inclusion and exclusion criteria, and use of validated measures to diagnose PTS, recurrent VTE and to measure QoL. To prevent unblinding of study nurses, patients are instructed not to wear ECS on the day of their study visits. While it is possible that patients may be able to distinguish active from inactive ECS, this is minimized by (1) using inactive ECS, developed by the manufacturer, that appear identical to active ECS, and (2) recruiting patients with a first DVT, i.e. likely to be "ECS-naïve". In addition to such pre-trial design features, we will assess the blinding procedures by asking patients, investigators and research nurses at the end of the trial (i.e. at 2 years or at time of study termination) if they were aware of the treatment assignment.

Study patients are followed for 2 years after enrollment. The procedures at each visit are shown in Table 1. At any time during the study, if a patient has symptoms or signs suggestive of recurrent VTE, he contacts the study team for medical assessment, at which time recurrent VTE will be ruled in or ruled out. Similarly, if an adverse event occurs, the patient contacts the study team for evaluation. If a patient withdraws from the study, a Study Termination form is completed to account for withdrawal, which will document the reason(s) for withdrawal. If a patient dies, a Death Form is completed which documents the cause(s) of death, further classified as VTE likely or unlikely. Throughout study follow-up, co-interventions are recorded (e.g. diuretics, analgesics, exercise). While not encouraged, any temporary use of elastic bandages/wraps or active stockings during the acute phase of DVT is systematically tracked.

**Table 1 T1:** Details of study visits and telephone calls

** *Enrollment visit* **
• The nurse completes the baseline form (inclusion/exclusion criteria, demographic and clinical variables, results of objective tests for DVT), PTS scale and pain scale
• The patient self-completes the QOL form
• The nurse performs the leg measurements to size the stockings
• The nurse teaches patients how to apply (using a plastic leg model) and care for stockings (handling, washing), and reinforces the importance of daily use
• Study stockings are supplied to the patient (within a few days after enrollment)
• A venous blood sample is taken for markers of inflammation
**2-week telephone call**
• The nurse reinforces the importance of wearing stockings daily
• Bleeding/Other Adverse Event form and pain scale are completed
For the following visits, the patient does not wear study stocking to prevent unblinding of study nurse:
**1-month visit**
• The nurse completes the follow-up form (includes data on symptoms and signs of PTS, suspected recurrent VTE, compliance with stockings, pain scale)
• The patient self-completes the QOL form
• Bleeding/Other Serious Adverse Event form is completed
• A venous blood sample is taken for markers of inflammation and genetic thrombophilia
• The nurse reinforces the importance of wearing stockings daily

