**2-month telephone call**
• Same as the 2-week telephone call

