**1-year visit**
• Same as 6-month visit except no blood sampling
• A venous ultrasound is performed to assess reflux

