### Primary and secondary outcome measures

The primary outcome measure is the incidence of PTS during 2 year follow up. PTS will be diagnosed at the 6 month visit or later if the patient reports pain and swelling of ≥ 1 month's duration that is typical in character (worse at the end of the day or with prolonged sitting or standing, and better after a night's rest and leg elevation), and that is present ≥ 6 months after the acute DVT [52]. Patients diagnosed with PTS will be considered to have reached the study endpoint. Severity of PTS will be graded according to the Villalta scale [53], a clinical post-thrombotic syndrome measure that rates the severity of five patient-rated symptoms and six clinician-rated clinical signs [53]. A Villalta score of 5–9 represents mild post-thrombotic syndrome; 10–14, moderate post-thrombotic syndrome; and > 15 or presence of a venous ulcer, severe post-thrombotic syndrome [53].

Secondary outcomes measures include:

• Reflux: Reflux will be assessed and quantified in a standardized fashion by venous ultrasound [52,56].

• Recurrent VTE: Objective tests and validated algorithms will be used to diagnose recurrent DVT and PE, as described previously [57-59], and all events and deaths will be independently and blindly adjudicated. Death from VTE will be assessed as 'likely' or 'unlikely' after review of the death certificate, patient chart, autopsy report (where available) and by contacting the treating physician.

• Bleeding: Clinically suspected bleeding events will be documented by recording the clinical event and results of any objective diagnostic testing performed. Bleeding will be defined as major if it is clinically overt and associated with a fall in hemoglobin of 20 g/L or a need for transfusion of ≥ 2 units of red blood cells; if it was intracranial or retroperitoneal; or if it warranted the permanent discontinuation of anticoagulation. Less severe clinically overt bleeding which is considered abnormal will be classified as minor.

• Markers of inflammation: C-reactive protein will be assayed using a nephelometric assay. IL-6, IL-8 and MCP-1 will be measured using commercial ELISA kits which include plasma controls (Biosource Europe SA, Nivelles, Belgium). At the time of blood draw for markers of inflammation, data will be recorded on time of day, type and duration of heparin use, concomitant medications and medical conditions.

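### As Table 1 is written, non-serious, non-bleeding adverse events are asked about only at the two early telephone calls and not after month 2 of 24

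*Protocol article*

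**What the plan says.** Table 1 of the protocol article names an adverse event form at every contact after enrollment, but not the same one.

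- **2-week call:** "Bleeding/Other Adverse Event form and pain scale are completed". The 2-month call is defined by reference: "Same as the 2-week telephone call".
- **1-month visit:** "Bleeding/Other Serious Adverse Event form is completed". The 6-month and 2-year visits carry the same entry. The 1-year and 18-month visits take it over by reference: "Same as 6-month visit except no blood sampling".

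Other sections of the article bear on capture:

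- **Study procedures** provides for unscheduled reporting: "Similarly, if an adverse event occurs, the patient contacts the study team for evaluation". This is not limited to serious events.
- **Study procedures** also has a termination form for withdrawals, "which will document the reason(s) for withdrawal".
- **Primary and secondary outcome measures** defines a minor class of bleeding: "Less severe clinically overt bleeding which is considered abnormal will be classified as minor".
- **Table 1, 1-month visit**, describes the follow-up form used at the visits: it "includes data on symptoms and signs of PTS, suspected recurrent VTE, compliance with stockings, pain scale".

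The article does not say why the form name differs between calls and visits.

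**The concern.** The harms one would expect from a stocking worn all day for two years are mostly non-serious: skin irritation, discomfort, poor fit. The two arms differ sharply in compression (30–40 mm Hg against 5 mm Hg at the ankle, under Current trial design). Such problems could therefore differ by arm, and they could affect compliance.

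If the form names mean what they say, the schedule stops asking about these events after the 2-month call. It does not ask at the later visits, including those where the leg is re-measured and new stockings are supplied. What is known about tolerability after that point would depend on who chooses to call.

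The primary efficacy comparison is not affected. At stake is a complete and even comparison of non-serious harms between arms over the full period of wear.

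**Working it through.** No sample size, power or error-rate figure is involved, and the plan states no figure of its own to reproduce. The check sets the entries side by side and counts contacts.

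**Step 1: contacts.** The Abstract gives 6 clinic visits and 2 calls, so 6 + 2 = 8. One visit is enrollment, for which Table 1 lists no adverse event form. Post-enrollment contacts: 8 − 1 = 7.

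**Step 2: form named at each contact.**

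| Contact | Type | Scope of the named form |
|---|---|---|
| 2 weeks | call | bleeding and other events, any grade |
| 1 month | visit | bleeding and other serious events |
| 2 months | call | as at 2 weeks |
| 6 months | visit | bleeding and other serious events |
| 12 months | visit | as at 6 months |
| 18 months | visit | as at 6 months |
| 24 months | visit | bleeding and other serious events |

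Unrestricted: 2 of 7, both calls. Limited to serious events apart from bleeding: 5 of 7, all visits. The 1-month entry alone costs little, since the 2-month call can pick up what it leaves out. The gap starts after month 2.

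**Step 3: time without scheduled solicitation.** Follow-up is 24 months and the last unrestricted contact is at month 2. (24 − 2)/24 = 22/24 = 91.7%, about 92%. This is a share of follow-up time.

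**Step 4: can it become a share of events?** Let f be the fraction of non-serious, non-bleeding events that begin after month 2, and r the fraction of those that patients report unprompted and that are then recorded. If events up to month 2 are all captured, the share missed is f × (1 − r). The article gives neither f nor r. Two assumptions show the range:

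- Constant onset: f = 22/24 = 92%, so the share missed runs from 0% (r = 1) to 92% (r = 0).
- Half of events begin by month 2: f = 50%, so it runs from 0% to 50%.

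The range is too wide to support any statement about how many events are lost.

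**Step 5: do the other routes close the gap?**

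- *Patient-initiated reports* cover any event, but need the patient to act. Mild irritation is the kind of problem a patient may not call about. The text says such events are evaluated but names no form for recording them.
- *Bleeding* is captured at any severity, but is not the characteristic harm of a stocking.
- *The follow-up form* records leg symptoms and signs as features of PTS. The Background section lists pain, swelling and eczema among those features, so a reaction to the stocking could be scored as disease rather than recorded as a harm.
- *Withdrawal reasons* catch only problems that end participation.

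None of these systematically asks about non-serious stocking problems after month 2.

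**The case against.** The strongest reply is that this is a condensed article and that the two near-identical labels are one form loosely named. The case report forms are not shown, and the article does not settle the question. That stands as a possibility. However, the word that separates the labels is absent at both calls and present in all three visit entries that are written out. If there is one form, Table 1 misdescribes it; if there are two, the gap is real. Either way the entries need reconciling.

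A second reply is that broad collection early, then serious events plus open reporting, is a recognisable design choice. That is fair. The protocol lists no tolerability aim, and the definitive data it promises in the Abstract concern PTS, DVT recurrence, cost-effectiveness and quality of life. But the article does not present the difference as a choice or give a reason for it.

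A reader might also go further and infer that the visits collect nothing but serious events, or that most harms of stocking wear go uncounted. The documents do not support either. The visit form also covers bleeding, for which a minor class exists, and the follow-up form records leg symptoms, signs and pain. Patients contact the team about any adverse event, and with no event rates given, a claim about most harms cannot be shown. Nor should the instruction not to wear stockings to visits count against the plan: it is a deliberate measure to keep the nurses blinded.

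**Conclusion.** The narrow point holds. As Table 1 is written, non-serious, non-bleeding adverse events are solicited at 2 of 7 post-enrollment contacts and not after month 2. For 22 of 24 months (92% of follow-up time) their capture rests on patient-initiated reports with no named recording form.

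This assumes that the form names describe the content of the forms, which the article neither confirms nor denies. The 92% must not be read as a share of events missed, which cannot be computed from the document. The matter is worth correcting because the compared stockings differ in compression and are worn for two years. It bears on the tolerability comparison and leaves the primary analysis untouched.

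**What to change.** Reconcile the Table 1 entries from the 2-week call to the 2-year visit. Then:

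1. Name one form, the unrestricted one already used at the calls, at all seven post-enrollment contacts, for serious and non-serious events alike. If only one form exists, correct its name in Table 1.
2. Include an item on stocking-related skin or leg problems. At the visits, complete it after the PTS rating so that it does not influence that rating.
3. State under Study procedures that patient-initiated reports are recorded on the same form.
4. Report these events by arm.

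The cost is a few minutes per visit and more non-serious entries to collect and clean. No extra visits or staff are needed.

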**2-month telephone call**
• Same as the 2-week telephone call
**6-month visit**
• The nurse completes the follow-up form
• The patient self-completes the QOL form
• Bleeding/Other Serious Adverse Event form is completed
• Leg measurements are taken, and a new pair of stockings is supplied
• A venous blood sample is taken for markers of inflammation, d-dimer and coagulation-based assays
• The nurse reinforces the importance of wearing stockings daily

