**Discussion:**

The SOX Trial will be the largest study and the first with a placebo control to evaluate the effectiveness of ECS to prevent PTS. It is designed to provide definitive data on the effects of ECS on the occurrence and severity of PTS, as well as DVT recurrence, cost-effectiveness and quality of life. This study will also prospectively evaluate the predictive role of biomarkers that are reflective of putative underlying pathophysiological mechanisms in the development of clinical PTS. As such, our results will impact directly on the care of patients with DVT.

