For the secondary outcomes valvular reflux, recurrent VTE, death from VTE, venous ulcer, major bleeding, and severity of PTS, rates in the two intervention groups will be described, and between-group differences explored in similar regression procedures. For differences in mean quality of life scores between intervention groups, analysis of variance incorporating treatment and center will be used. A difference of 4–5 points between groups is considered to be clinically meaningful. Analysis of covariance with adjustment for age, sex and comorbidity will also be used to compare quality of life between groups. For the biomarker variables, univariate analysis will be used to determine the strength of association between each biomarker variable and the occurrence of PTS. For genetic markers, heterozygotes and homozygotes will be analyzed together, given the rarity of homozygotes. IgG, IgM and lupus anticoagulant results will be dichotomized as normal or abnormal. Factor VIII, D-dimer and markers of inflammation will be analyzed both as continuous data and as proportion of values exceeding the upper 90^th ^percentile. For binary and nominal data, the appropriate chi-square tests will be used to examine the respective crude associations, and for continuous variables, the unpaired 2-tailed t-test. To examine adjusted associations, multiple logistic regression analyses will be performed in which the dependent variable is the presence of PTS. The independent variables to be tested are markers of thrombophilia, D-dimer, and levels of CRP, IL-6, IL-8 and MCP-1. Other variables of interest (for interaction and/or confounding) are age, sex, ethnicity, comorbid illness, allocation to active ECS, type and duration of heparin and warfarin use, type of DVT (unprovoked vs. secondary; anatomic extent of DVT), and recurrent DVT during follow-up. The analyses will aim to (1) identify the strength of the association between relevant biomarkers, other relevant explanatory variables and PTS; and (2) explore relevant interactions. Similarly, multiple linear regression will be performed in which the dependent variable is the severity of PTS, as measured by the Villalta scale.

An interim analysis for efficacy will be performed when half of the subjects have completed 2 years of follow-up. The analysis plans call for a Lan-DeMets alpha spending approach with an O'Brien Fleming boundary [70].

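### D-dimer is drawn only at the 6-month visit, where PTS can first be diagnosed, yet is modelled against all PTS; for cases found then, the result is association, not prediction

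*Protocol article*

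**What the plan says.** All references are to the protocol article.

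- **Blood sampling (Table 1).** Enrollment: "A venous blood sample is taken for markers of inflammation". One month: "A venous blood sample is taken for markers of inflammation and genetic thrombophilia". Six months: "A venous blood sample is taken for markers of inflammation, d-dimer and coagulation-based assays". One year and 18 months: "Same as 6-month visit except no blood sampling". No draw is listed at 2 years. D-dimer and coagulation-based assays therefore appear once, at 6 months.
- **Outcome (Primary and secondary outcome measures).** "PTS will be diagnosed at the 6 month visit or later if the patient reports pain and swelling of ≥ 1 month's duration". The 6-month visit is the earliest at which a patient can become a case.
- **Model (Statistical analysis).** "multiple logistic regression analyses will be performed in which the dependent variable is the presence of PTS". D-dimer, thrombophilia markers and four inflammatory markers are the independent variables. Cases found at 6 months are neither excluded nor separated.
- **Purpose.** The Abstract says "This study will also prospectively evaluate the predictive role of biomarkers". The end of the Background and the Discussion also speak of a prospectively assessed predictive role.

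**The concern.** A prognostic claim needs the marker to be measured before the outcome. Here the only D-dimer value is taken on the day the first cases are declared, and those cases have by definition been symptomatic for a month or more. Pooling them with later cases in one logistic model mixes two quantities: whether D-dimer at 6 months forecasts later PTS, and whether patients who already have PTS differ in D-dimer. If PTS itself raises D-dimer, the pooled odds ratio departs from 1 even when the marker forecasts nothing.

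The reverse direction is conceivable on the article's own account of the disease, which includes persistent venous obstruction, leakage of plasma and leukocytes, and tissue hypoxia. At stake is the meaning of a positive Bio-SOX result, which the Discussion says could lead to therapies aimed at these markers. The randomized comparison of stockings is not affected.

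**Working it through.** **1. The plan's own figures.** PTS at 30% versus 20%, two-sided alpha 0.05 and 80% power give 294 per arm, 588 in total, close to the stated 600. Then 600/(1 − 0.25) = 800. The biomarker claim of more than 80% power at an odds ratio (OR) of 2.0 also reproduces with 600 patients and overall PTS risk (30% + 20%)/2 = 25%, provided the marker is common enough: 87% with 20% exposed and 95% with 50% exposed. None of these figures deals with timing.

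**2. Timing.**

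| Marker | First value listed | Before the first possible PTS diagnosis? |
|---|---|---|
| CRP, IL-6, IL-8, MCP-1 | Enrollment, then 1 and 6 months | Yes, for the first two values |
| Genotypes | 1 month (fixed at birth) | Yes |
| D-dimer | 6 months | No, same visit |
| Factor VIII, lupus anticoagulant | 6 months, as coagulation-based assays | No, same visit |
| IgG/IgM antiphospholipid antibodies | Not named in Table 1 | Inferred: they share an outcome-section bullet with the coagulation assays, and no other draw is listed |

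This loss of temporal order follows from the text alone. Steps 3 and 4 need assumptions.

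**3. Possible false-positive rate, continuous marker.** Take 600 patients, 150 with PTS (25%), and no true predictive value. Let *s* be the share of all cases already present at 6 months and *d* the amount, in SD, by which existing PTS raises the marker. The article gives neither.

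- Mean difference, cases minus non-cases: *s* × *d*
- Standard error: √(1/150 + 1/450) = 0.094 SD
- *z* = *s* × *d* / 0.094
- Rejection probability: P(Z > 1.96 − *z*) + P(Z < −1.96 − *z*)

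Example: *s* = 0.5 and *d* = 0.1 give 0.05/0.094 = 0.53, hence about 8%.

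| Shift *d* | *s* = 30% | *s* = 50% | *s* = 70% |
|---|---|---|---|
| 0 | 5% | 5% | 5% |
| 0.1 SD | 6% | 8% | 12% |
| 0.3 SD | 16% | 36% | 61% |
| 0.5 SD | 36% | 76% | 96% |

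Simulated logistic regressions (800 studies per scenario) agree for the 0.3–0.5 SD rows: 17–33%, 37–74% and 61–96%. Restricted to patients free of PTS at 6 months, the simulated rate stays near nominal (4–7%).

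**4. Possible spurious odds ratio, marker cut at the 90th percentile.** Assume 10% have a raised marker among non-cases and among later cases (true OR 1.0), and a fraction *q* among cases present at 6 months. Raised cases = 150 × [*s* × *q* + (1 − *s*) × 0.10]. Non-cases split 45 raised, 405 not. For *s* = 0.5 and *q* = 0.20, raised cases = 22.5 and OR = (22.5/127.5)/(45/405) = 1.59.

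| Share *s* | *q* = 15% | *q* = 20% | *q* = 30% |
|---|---|---|---|
| 25% | 1.14 | 1.29 | 1.59 |
| 50% | 1.29 | 1.59 | 2.25 |
| 75% | 1.43 | 1.91 | 3.00 |

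**5. Cost of restricting to later PTS.** Remove the 150 × *s* early cases from both numerator and denominator, solve the exposed and unexposed risks from OR 2.0 and the remaining overall risk, and apply the two-proportion power formula.

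| Share *s* | Later cases / patients | Power, 10% exposed | Power, 50% exposed |
|---|---|---|---|
| All PTS counted | 150/600 | 68% | 95% |
| 25% | 112/562 | 61% | 90% |
| 50% | 75/525 | 51% | 78% |
| 75% | 37/487 | 36% | 51% |

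**The case against.** **The analysis plan may settle this.** It is not shown, and pairing a marker's time point with the timing of the outcome is commonly fixed there. The data would allow it, because PTS is assessed by visit. This stands in part. But the article itself fixes the draw, the earliest diagnosis visit and the dependent variable, and read together these do not support its predictive claim for D-dimer.

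**The stated aims are modest.** The Statistical analysis section speaks of strength of association, and the secondary aim of influence. That is fair, but the Abstract, Background and Discussion claim prediction. The sample-size section calls only the inflammatory-marker analysis largely exploratory.

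**No reverse effect is documented.** This stands. No passage says that PTS raises D-dimer, and the Background gives only the forward direction. A reader might infer from the upper figures above that the planned model will usually produce a false finding. The documents do not support that: the 0.3–0.5 SD shift is assumed, and at 0.1 SD the excess over 5% is small.

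**Not all markers are equally exposed.** A reader might extend the point to every marker. That goes too far:

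- Factor VIII elevation is described in the Background as an inherited risk factor, independent of acute-phase markers, so reverse causation is a weaker concern there.
- The antiphospholipid ELISA is placed in the 6-month draw only by inference.
- Inflammatory markers have enrollment and 1-month values, the power statement refers to initial values, and the article does not say that the 6-month value enters the PTS model.
- Genotype cannot be changed by PTS.

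**The repair changes the question.** This also stands: restricting to later PTS discards early cases, which would carry signal if a persistent marker truly drives early PTS.

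**Conclusion.** The point holds in a limited form. For D-dimer, and less seriously for Factor VIII and other coagulation-based assays, the plan as written cannot support a predictive claim for cases diagnosed at 6 months, because the only sample follows symptom onset. That conclusion rests on the text and needs no assumption.

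Whether the pooled association is inflated, and by how much, is unknown. It depends on the share of cases present at 6 months and on the effect of PTS on the marker, neither of which the article gives. With assumed shares of 30–70%, the false-positive rate runs from 5% (no shift) through about 6–12% (0.1 SD) to 17–96% (0.3–0.5 SD).

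The matter concerns one secondary aim and should be corrected before the biomarker analysis. It does not bear on the primary outcome or the treatment comparison.

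**What to change.** In the biomarker analysis text:

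1. For D-dimer, and for any other marker whose 6-month value is used, base the predictive claim on a 6-month landmark analysis: include patients without PTS at that visit, and take PTS first diagnosed after it as the outcome.
2. Report cases found at 6 months, and the all-PTS model, separately and as association only.
3. Use enrollment and 1-month inflammatory values, and genotype, against all PTS.
4. State at which draw the antiphospholipid ELISA is taken.

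No new visits or blood are needed. The cost is fewer events and lower power, as in step 5 of the working, and the plan should say so. With 10% exposed, the smallest odds ratio detectable with 80% power becomes about 2.4, 2.7 or 3.5 if 25%, 50% or 75% of cases are present at 6 months (assumed shares, 600 patients). The plan should also say that the landmark result does not cover early PTS. Assaying D-dimer in the enrollment or 1-month samples would avoid both costs, if suitable plasma was kept; the article does not say whether it was.
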